## Abstract

**Background:**

Acute mountain sickness (AMS) is a cluster of symptoms that commonly occur in those ascending to high altitudes. Symptoms can include headaches, nausea, insomnia and fatigue. Exposure to high altitude can also lead to high-altitude cerebral oedema (HACE), which is a potential cause of death whilst mountaineering. Generally, AMS precedes the development of HACE. Historical studies have demonstrated the effectiveness of regular dexamethasone administration in reducing the symptoms of AMS. However, the mechanism by which dexamethasone works to reduce symptoms AMS remains poorly understood. Further studies, simulating altitude using hypoxic tents, have characterised the effect of prolonged exposure to normobaric hypoxia on cerebral oedema and blood flow using MRI. This randomised trial assesses the effect of dexamethasone on hypoxia-induced cerebral oedema in healthy adult volunteers.

**Methods/design:**

D4H is a double-blind placebo-controlled randomised trial assessing the effect of dexamethasone on hypoxia-induced cerebral oedema. In total, 20 volunteers were randomised in pairs to receive either 8.25 mg dexamethasone or normal saline placebo intravenously after 8 h of hypoxia with an FiO_2_ of 12%. Serial MRI images of the brain and spinal cord were obtained at hours 0, 7, 11, 22 and 26 of the study along with serum and urinary markers to correlate with the severity of cerebral oedema and the effect of the intervention.

**Discussion:**

MRI has been used to identify changes in cerebral vasculature in the development of AMS and HACE. Dexamethasone is effective at reducing the symptoms of AMS; however, the mechanism of this effect is unknown. If this study demonstrates a clear objective benefit of dexamethasone in this setting, future studies may be able to demonstrate that dexamethasone is an effective therapy for oedema associated with brain and spinal cord ischaemia beyond AMS.

**Trial registration:**

Clinicaltrials.gov, NCT03341676. Registered on 14 November 2017.

## Background

Acute mountain sickness (AMS) is a cluster of symptoms that commonly occur in those ascending to high altitudes (>1500 m), including headaches, nausea, insomnia and fatigue [1]. Exposure to high altitude can also lead to the more dangerous high-altitude cerebral oedema (HACE), which is a potential cause of death whilst mountaineering. Whether HACE and AMS belong to the same pathophysiological spectrum is a matter of debate, although generally AMS precedes the development of HACE.

Magnetic resonance imaging (MRI) studies have demonstrated the impact of prolonged periods at altitudes of up to 4350 m on cerebral white matter volume and cerebral blood flow. Hypoxia is associated with a compensatory increase in cerebral blood flow and a subsequent increase in brain volume, which can be demonstrated through MRI [2]. The increasing use of hypoxic tents to induce AMS has allowed interval imaging and a clearer demonstration of both the timing and patterns of oedema development in the brain [3]. MRI is useful for monitoring the brain during these periods, as directly measuring the intracranial pressure is difficult to do or justify in healthy volunteers whereas the intracranial pressure can be inferred indirectly using the change in the volume of different intracranial tissues [3]. Kallenberg et al. used diffusion-weighted imaging (DWI) to demonstrate that AMS sufferers have a decreased apparent diffusion coefficient (ADC), a measure of how freely water can move between tissues [4–6]. The drop in ADC suggests cytotoxic oedema is an important component of AMS. This mechanism has many similarities with the accepted pathophysiology of cytotoxic oedema during cerebral ischaemia [7]. Compared to healthy tissue, the ischaemic spinal cord, like the brain, also shows a drop in ADC on DWI accompanied by hyperintensity on T2-weighted imaging [8–11]. Zhang [11] used canine models to demonstrate that changes in DWI and T2-weighted imaging are visible within an hour of inducing spinal cord ischaemia.

Double-blind studies simulating altitude have already demonstrated the effectiveness of regular dexamethasone administration in reducing the symptoms of AMS. Johnson et al. compared 6 hourly dexamethasone (4 mg dose) to a placebo in 16 men exposed to a simulated altitude of 4570 m using a hypobaric chamber [12]. A meta-analysis by Tang et al. [13] of using oral dexamethasone to treat AMS calculated an odds ratio of 6.03 (95% confidence interval, 2.23–21.00, *p* ≥ 0.05) compared to a placebo.

Multiple peripheral serum biomarkers of cerebral or blood–brain barrier dysfunction are currently under investigation; however, none have previously been applied to AMS and HACE. Glial fibrillary acidic protein (GFAP) is an intermediate filament protein that is upregulated in astrocytes following neuronal injury. There is good experimental correlation with neurological damage after a stroke or traumatic brain injury. Purine nucleosides (adenosine, inosine and hypoxanthine) have also been found to be sensitive early markers of ischaemic brain events [14, 15]. α-1 acid glycoprotein has recently been shown to act as a more sensitive marker of proteinuria than the more widely utilised urinary protein, albumin [16]. In animal models, the presence of proteinuria has been demonstrated to precede cerebral oedema and has been demonstrated to modulate the permeability of the blood–brain barrier [17, 18], as well as correlating with exposure to hypoxia [19].

Despite evidence for its efficacy, the mechanism behind the effect of dexamethasone remains poorly understood. Therefore, it has not been validated as a true therapeutic solution to AMS or HACE. This study aims to provide evidence of the mechanisms of action and therapeutic potential of dexamethasone for the treatment of symptomatic AMS and other causes of cerebral and spinal cord oedema and to investigate and correlate changes in peripheral serum biomarkers in response to hypoxia with radiological findings.

## Methods/design

### Study design

D4H is a phase-I double-blind placebo-controlled randomised control trial assessing the effect of dexamethasone on hypoxia-induced cerebral oedema in healthy adult volunteers.

### Hypothesis

A single dose of intravenous dexamethasone given after 8 hours in normobaric hypoxia at 12% inspired oxygen concentration (FiO2) reduces the incidence or severity of the symptoms of AMS, as determined by MRI changes due to cerebral oedema.

### Primary objective

To identify any measurable differences in:
Lake Louise scoresprespecified MRI parametersfollowing prolonged normobaric hypoxia after administration of a single dose of intravenous dexamethasone compared to a placebo.

### Secondary objectives

To measure the integrity of the blood–brain barrier and astrocyte dysfunction using proxy measurements (serum purine levels and GFAP) and correlate these with primary outcome measures.To correlate proteinuria with the primary outcome measures.

#### Sample size

Estimates from our previous observational study of MRI differences at normobaric hypoxia were used to determine the power [3]. It was assumed that dexamethasone will reverse outcome measures to their baseline values. Powers for pairwise comparisons at 22 h for three different significance levels (0.05, 0.10 and 0.20) and for three outcome measures that showed change at 22 h from baseline in the observational work were calculated by assuming that the data are normally distributed, (Table 1). Since most of the other outcomes showed smaller differences, it was decided to test hypotheses at 20% significance and make this study a pilot study.

**Table 1 Tab1:** Power for different outcomes and significance levels

Outcome	Estimates from Sagoo et al. [3]		Power		
	Difference	Standard deviation	α = 0.05	α = 0.10	α = 0.20
Blood oxygen content, ml O_2_/dL blood	2.05	1.33	97	98	99
Whole-brain ADC × 10^–4^/mm^3^	0.5	0.45	78	86	93
Corpus callosum (genu) ADC × 10^–4^/mm^3^ (mean of right and left)	1.35	1.65	52	64	77

*ADC* apparent diffusion coefficient

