#### Trial oversight

Trial oversight is provided by the trial management group. The trial steering committee will meet regularly to review progress and the safety of the study. There is also an independent data management group. The study sponsor, UHCW, is a National Institute for Health Research facility. The study was reviewed after the first two participants to ensure the safety and quality measures were met. After 20 patients had completed the protocol, a preliminary analysis was performed, and if sufficient differences had been seen, the study would have been closed to recruitment. If not, recruitment will continue to 30 patients. All potential AEs, as defined by good clinical practice (AEs, SAEs or SUSARs), were compiled by the trial manager and statistician and reviewed by the sponsor. All Grade IV AEs, all SAEs and all SUSARs were reported to the trial management group within 24 h. Participant information will be held securely at the trial sponsor site until study closeout, when they will be transferred to a third-party storage facility with appropriate security, and fire and flood provisions.

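### Table 1 gives powers with no number per arm and no named test; they fit neither 20 nor 30 volunteers, and both ADC powers are too high for 20

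*Protocol article*

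**What the plan says.** Sample size, with Table 1, is the only place in the protocol article that gives power. It takes differences and standard deviations from the group's earlier observational study. On the effect it says: "It was assumed that dexamethasone will reverse outcome measures to their baseline values". The powers "were calculated by assuming that the data are normally distributed", and are described as "Powers for pairwise comparisons at 22 h for three different significance levels (0.05, 0.10 and 0.20"). For difference, standard deviation, and power at 0.05, 0.10 and 0.20, the rows are:

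- blood oxygen content: "Blood oxygen content, ml O_2_/dL blood 2.05 1.33 97 98 99"
- whole-brain ADC: "0.5 0.45 78 86 93"
- genu ADC: "1.35 1.65 52 64 77"

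The section gives no number per arm and does not name the test.

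Trial size appears elsewhere. The Abstract says "In total, 20 volunteers were randomised in pairs". Trial oversight describes a preliminary analysis after 20 have completed and then, should differences be insufficient, an extension: "If not, recruitment will continue to 30 patients". A total of 24 appears nowhere, and no dropout allowance is stated that would link 20 or 30 to another number.

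**The concern.** A power is a statement about a particular number of volunteers and a particular test. Table 1 omits both, so a reader will attach its figures to the 20 volunteers named in the Abstract. If the figures were calculated for a larger number, the trial at 20 is weaker than it says.

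The two ADC rows matter most, because they are the only MRI outcomes with any stated power and MRI parameters are part of the primary objective. A null result on genu ADC at the 20% level would be read against a stated 23% chance of missing the assumed effect (100 − 77). At 10 per arm that chance is nearer 30%, even though the assumed effect is a full return to baseline.

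**Working it through.** **Inputs.** Differences and standard deviations are from Table 1. Two-sided testing is implied by the Statistical analysis plan section, which tests a mean difference of zero. Allocation of 1:1 is assumed, since no ratio is stated.

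**Standardised differences.** d = difference / SD:

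- blood oxygen content: 2.05 / 1.33 = 1.541
- whole-brain ADC: 0.5 / 0.45 = 1.111
- genu ADC: 1.35 / 1.65 = 0.818

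**Formulas.** For n per arm, the z-test (SD treated as known) has power ≈ Φ(d√(n/2) − z), with z = 1.960, 1.645 and 1.282 for alpha 0.05, 0.10 and 0.20. The t-test uses the noncentral t distribution with noncentrality d√(n/2) and 2n − 2 degrees of freedom.

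**Reproducing the table.** With n = 12, √(n/2) = 2.449. For whole-brain ADC, 1.111 × 2.449 = 2.722, so power is Φ(0.762), Φ(1.077) and Φ(1.440), or 77.7, 85.9 and 92.5%. All rows, two-sided z-test, 12 per arm (%):

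| Outcome | Recomputed | Stated |
|---|---|---|
| Blood oxygen content | 96.5 / 98.3 / 99.4 | 97 / 98 / 99 |
| Whole-brain ADC | 77.7 / 85.9 / 92.5 | 78 / 86 / 93 |
| Genu ADC | 51.8 / 64.0 / 76.5 | 52 / 64 / 77 |

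All nine agree after rounding; the largest deviation is 0.49 point.

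**How unique that fit is.** A search over 4 to 30 per arm (z and t, one- and two-sided) found no other equal-arm two-sample design matching all nine after rounding. Designs with the same standard error do match: z with 10 v 15 (1/10 + 1/15 = 1/12 + 1/12 = 1/6), or a one-sample z with n = 6. A t-test with 13 per arm comes within one point, but gives 86.6, 64.9 and 77.9 where 86, 64 and 77 are printed.

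**Powers at the documented sizes** (two-sided, alpha 0.05 / 0.10 / 0.20, %):

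| Outcome | Stated | 10 per arm, t (18 df) | 10 per arm, z | 15 per arm, t (28 df) |
|---|---|---|---|---|
| Blood oxygen content | 97 / 98 / 99 | 90.3 / 95.2 / 98.1 | 93.1 / 96.4 / 98.5 | 98.3 / 99.3 / 99.8 |
| Whole-brain ADC | 78 / 86 / 93 | 65.2 / 77.2 / 87.4 | 70.0 / 79.9 / 88.6 | 83.6 / 90.7 / 95.7 |
| Genu ADC | 52 / 64 / 77 | 41.0 / 54.6 / 69.4 | 44.8 / 57.4 / 70.9 | 58.1 / 70.6 / 82.3 |

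At 10 per arm the largest gap is 12.8 points by t-test (78 − 65.2) and 8.0 by z-test (78 − 70.0). A one-sided reading at 10 per arm does not rescue the table: it misses by up to 6.4 points (t) or 6.8 (z).

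**Pairs at 30.** The Randomisation section puts volunteers attending on the same day in the same arm. Thirty volunteers make 15 pairs, so intact pairs give 14 v 16 at best. That is equivalent to 2 × 14 × 16 / 30 = 14.9 per arm, so the last column barely changes.

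**The case against.** **Was the trial planned for 24?** A reader might infer from the exact fit that the powers belong to a 12-per-arm trial. The document does not establish that. It names neither number nor test, other designs give the same nine values, and 24 lies between the two sizes it does give. What stands is narrower: the table cannot be tied to 20 or 30 at 1:1.

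**Is every power overstated?** Only at 20, and unevenly. Blood oxygen content at the 20% level falls from 99 to 98.1 (t) or 98.5 (z), which is trivial. At 30 all nine printed values are too low. A null result after the extension would be read at about 82% for genu ADC, not 77%.

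**Is genu power at 20 at most 69%?** That is too firm. The known-SD figure is 70.9%, and the planned analysis is a mixed model over all time points, chosen because a 22 h t-test is inefficient. If baseline adjustment alone reduced the variance by 1 − ρ², then 10 per arm would match 12 when 1 − ρ² = 10/12, so ρ ≈ 0.41. Against that, same-day pair allocation could lower power. The document gives neither a baseline correlation nor an ICC, so neither effect can be credited. Table 1 is in any case described as a comparison at 22 h, not as mixed-model power.

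**Does this undermine the 20% level?** No. The section chooses that level because most other outcomes showed smaller differences. Lower power would strengthen that argument. The section also does not say that the trial size was derived from the table.

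**Should the blood oxygen row go, or the Lake Louise score be given a power statement?** Those are separate preferences about content, not errors in these figures.

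**Conclusion.** The point holds as an arithmetic and reporting error. Table 1 omits the number per arm and the test, and its values match neither documented size. For the 20 volunteers randomised, both ADC powers are overstated whichever test is used:

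- At the chosen 20% level, by about 4 to 6 points for whole-brain ADC (93 against 88.6 or 87.4) and 6 to 8 points for genu ADC (77 against 70.9 or 69.4).
- At 5%, by 8 to 13 points for whole-brain ADC (78 against 70.0 or 65.2) and 7 to 11 points for genu ADC (52 against 44.8 or 41.0).

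For 30 volunteers the table understates power.

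The conclusion assumes 1:1 allocation, two-sided tests, Table 1's own differences and standard deviations, and volunteers analysed as independent at 22 h. It does not depend on what design actually produced the table. It does not show that the trial needs more volunteers, nor that the pilot designation or the 20% level is wrong.

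**What to change.** In Sample size, state the number per arm and the test behind Table 1. Restate the powers with the t-distribution for 20 volunteers (10 per arm), and add a column for 30 if the extension stays (about 15 per arm, or 14 v 16 with intact pairs). Rounded, at 0.05 / 0.10 / 0.20:

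- 20 volunteers: blood oxygen content 90 / 95 / 98, whole-brain ADC 65 / 77 / 87, genu ADC 41 / 55 / 69.
- 30 volunteers: blood oxygen content 98 / 99 / >99, whole-brain ADC 84 / 91 / 96, genu ADC 58 / 71 / 82.

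Add one sentence saying that these are powers for a 22 h comparison of independent volunteers. It should say that they allow neither for same-day pair allocation, which could lower power, nor for any gain from the mixed model. If the table was in fact calculated for some other number, say so and explain how that number relates to 20 and 30.

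The change costs a corrected table and a sentence or two. No extra volunteers are needed and the analysis does not change. The price is less favourable stated powers at 20.

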#### Inclusion and exclusion criteria

Subjects between the ages of 18 and 35 with a body mass index <30 kg/m^2^ who have not been to an altitude greater than 1500 m within 12 weeks were invited to participate. They provided written informed consent, which was obtained by a medically qualified doctor, as delegated by the chief investigator.

Patients with any systemic illness, currently pregnant or breastfeeding, or with recorded contra-indications to taking dexamethasone or having an MRI were excluded. Patients with a medical history of hypertension, untreated respiratory disease, glaucoma, epilepsy, peptic ulcer, recent surgery or known intra-cranial pathology were also ineligible.

#### Randomisation

Once eligibility had been confirmed, participants were allocated to the treatment or placebo group via block randomisation. The participants were randomised in sex-matched pairs and the randomisation sequence allocated participants attending on the same day to the same study arm to prevent unintentional unblinding of participants or investigators during the visit. The randomisation list was generated by computer by a statistician. Except in the case of an adverse event (AE) requiring unblinding, only the statistician who generated the list and the pharmacist are not blinded to study allocation. They are not members of the trial management group.

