##### Statistical analysis plan

As in Sagoo et al. [3], it thought plausible to assume that the outcomes would be normally distributed. We will assess this assumption using the residuals from models that assume the data are normally distributed. If the residuals are not normally distributed, we will transform the raw data and repeat the normality assumption check.

Ultimately the primary aim of the study is to compare outcomes between placebo and dexamethasone groups at 22 h. The comparisons could be made by performing *t*-tests using data collected at 22 h. This is, however, inefficient and so potentially to increase power, we will include outcome measures for all time points. To account for the correlation among measurements taken from the same volunteer at multiple time points, we will analyse data by fitting linear mixed models. Separate linear mixed models will be fitted for different outcomes. Each linear mixed model will include a fixed term(s) for the time at which a measurement was taken, a fixed term for the treatment group of the volunteer and an interaction term for time and treatment group. The interaction term enables us to make inference for the mean difference between the placebo and dexamethasone groups at different time points. If there is an imbalance of a baseline characteristic, a fixed term for the characteristic will be included in the model. Outcome measurement profiles over time will be assessed first. If the relationship is approximately linear, a linear term for time will be fitted. If not, time will be taken as a categorical variable.

For data taken at 22 h, we will report the estimated mean differences, the 95% confidence interval for the mean differences of the primary outcome measures and *p* values to test the hypothesis that the mean difference is zero. As mentioned previously, because this is a pilot study, the hypothesis will be tested at a 20% significance level. Also, for the same reason, we will not adjust for multiple hypotheses (corresponding to different outcome measures).

The above analysis plan will be used if it is plausible to assume that the data are normally distributed. If a transformation does not achieve normality, we will use non-parametric methods such as the Mann–Whitney U test.

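### Sex-matched pairs go whole to one arm, so the matching widens chance sex imbalance between arms; sex should be a fixed term in every model, not one added only if imbalance is seen

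*Protocol article*

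**What the plan says.** The abstract says that "20 volunteers were randomised in pairs to receive either 8.25 mg dexamethasone or normal saline placebo". The Randomisation section says that "participants were allocated to the treatment or placebo group via block randomisation", and then: "The participants were randomised in sex-matched pairs and the randomisation sequence allocated participants attending on the same day to the same study arm". The reason given for the same-day rule is blinding: "to prevent unintentional unblinding of participants or investigators during the visit". That section gives no block size and no stratification by sex.

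The Trial oversight section fits two volunteers per visit day ("The study was reviewed after the first two participants to ensure the safety and quality measures were met") and leaves room for more pairs after the look at 20: "If not, recruitment will continue to 30 patients".

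On analysis, the section on baseline data names gender as a characteristic to be compared between groups by Fisher's exact test. The Statistical analysis plan section then says: "If there is an imbalance of a baseline characteristic, a fixed term for the characteristic will be included in the model". It gives no criterion for imbalance and does not name sex as a planned model term.

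**The concern.** Matching on a factor balances it between arms only when the matched members go to opposite arms. Here the two matched volunteers appear to share a visit day and hence an arm, so each allocation moves two people of one sex into one arm. Blocks of such pairs balance the number of pairs, not the sexes.

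The same-day rule alone does not cause this. If pairs were formed without regard to sex, allocating them whole would give the same distribution of sex splits as randomising individuals. The excess comes from making the pairs same-sex.

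Several outcomes in the Outcome measures section are absolute sizes or flows: brain and cerebrospinal fluid volume, artery diameter and flow, cord volume and length. If these differ by sex, an uneven sex split adds noise to the planned 22 h comparison between arms.

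**Working it through.** The plan states no figure to reproduce. Assumptions, since the protocol gives neither allocation ratio nor sex mix: 10 pairs, 5 per arm; 4, 5 or 6 male pairs; comparator, the same 20 people randomised singly, 10 per arm.

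**1. Spread of the imbalance, 5 male pairs.** Let k be the number of male pairs in one arm (hypergeometric).
- Pairs: Var(k) = 5 × 0.5 × 0.5 × 5/9 = 0.694. The difference in men is 4k − 10, with SD 4 × 0.833 = 3.33, so the SD of the difference in proportion male is 0.333.
- Singly: Var = 10 × 0.5 × 0.5 × 10/19 = 1.316. The SD of the difference is 2 × 1.147 = 2.29, or 0.229 as a proportion.
- Variance ratio: 0.333²/0.229² ≈ 2.1.
- Exact balance is impossible; the best split is 6 v 4. P(8 v 2 or worse) = 2 × (25 + 1)/252 = 0.206, against 0.023 singly.

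**2. With 6 male pairs (4 is symmetrical).** P(6 v 6) = C(6,3) × C(4,2)/252 = 120/252 = 0.476, so P(difference of at least 4 men) = 132/252 = 0.524, against 0.170 singly. Most of this is 8 v 4: 120/252 = 0.476.

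**3. What an imbalance-triggered term would catch.** Fisher's exact test: 8/10 v 2/10, p = 0.023; 8/10 v 4/10, p = 0.17. If Fisher at 5% were the trigger (an assumption), 8 v 2 is adjusted and 8 v 4 is not. At a 20% trigger both are adjusted.

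**4. Precision of the 22 h contrast, 5 male pairs.** Take a within-sex SD of 1 and a sex difference of δ SD (assumed 0.5, 1.0, 1.5).
- Unadjusted: SD = √(2/10 + δ²/9) = 0.48, 0.56, 0.67.
- Sex fitted: the variance is 0.2/(1 − r²), where r is the difference in proportion male. A 6 v 4 split (r = 0.2) gives 0.208; 8 v 2 (r = 0.6) gives 0.3125. Weighting by 200/250 and 50/250 gives 0.229, so SD = 0.48 whatever δ is. The two fully confounded draws (10 v 0) are left out, because sex cannot be fitted there.
- At δ = 1, fitting sex cuts the SD from 0.56 to 0.48. At δ = 0.5 there is no gain.

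**5. Error rate at the 20% level.** Simulated 22 h t-tests with no drug effect, 10 per arm, 5 male pairs, as an approximation to the mixed model:

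| Sex difference (SD) | Pairs ignored | Pair-level analysis |
|---|---|---|
| 0.5 | about 22% | about 20% |
| 1.0 | about 25% | about 20% |
| 1.5 | about 28% | about 20% |

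Randomising individuals gives 20% throughout.

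**The case against.** **The tempting stronger reading.** A reader might infer that the matching biases the dexamethasone comparison, or produces false positives even when pairs are analysed correctly. The documents do not support this. The expected sex difference between arms is zero. Sex is constant within a same-sex pair, so its effect is between-pair variance, which a pair-level standard error already carries; step 5 shows no inflation there. The excess error arises only if pairs are ignored, which is a separate question.

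**The 8 v 2 split.** A reader might take its 20.6% chance as the damage. But the protocol names gender as a baseline characteristic to compare, and Fisher's test gives p = 0.023, so its conditional rule would most likely bring sex into the model. With 5 male pairs the only milder split is 6 v 4. The split that could slip through, 8 v 4, needs 4 or 6 male pairs and a cut-off stricter than 17%. The only testing level the protocol states is 20%, and that is for outcomes.

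**Silence and purpose.** The article is condensed. The list may have been stratified by sex in a fuller document, which would remove most of the imbalance. Nor does the text say that the matching was meant to balance arms, or outright that the matched pair is the same-day pair. If matched partners were split across arms on different days, sex would be balanced. These points limit the claim about allocation; they do not remove the case for always fitting sex.

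**Change scores.** The Outcome measures section speaks of changes in volume, and the first scan supplies baseline values. If change is analysed, constant sex differences cancel. The planned model, however, takes outcome measures at all time points and compares arms at 22 h, and names no baseline value as a covariate.

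**Conclusion.** The point holds as a matter of precision and chance imbalance, not of directional bias. On the natural reading of the abstract and the Randomisation section, the matching does not balance sex and about doubles the variance of its imbalance between arms. The consequence is a noisier 22 h contrast on outcomes with a sex difference well above 0.5 SD (SD 0.56 against 0.48 at 1 SD), together with imbalances such as 8 v 4 that a 5% screen would leave unadjusted. Inflation of the 20% error rate, to about 22% to 28%, is conditional on the analysis also ignoring pairs.

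All this rests on assumed 1:1 allocation of 10 pairs, 4 to 6 of them male, no sex stratum, and sex differences of 0.5 to 1.5 SD; the documents give none of these figures. The remedy does not depend on them: sex was used to form the pairs and is already collected.

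**What to change.** 1. In the Statistical analysis plan section, include sex as a fixed term in every mixed model whatever imbalance is observed, and fix this before unblinding. Cost: one degree of freedom, and a negligible loss of precision where an outcome barely differs by sex. If an arm turns out to be all of one sex and the other arm all of the opposite sex, the term cannot be fitted and the report should say so. This applies even if recruitment is over or the list was stratified.
2. For any pairs still to be allocated, up to the 30 participants allowed in Trial oversight, randomise in separate blocks for male and female pairs and keep the same-day, same-arm rule. Cost: a second computer-generated list; with so few pairs, blocks may end incomplete and the arms may differ by a pair or two.
3. In the Randomisation section, state whether the sex-matched pair is the same-day pair, and whether the blocks were stratified by sex. Cost: one sentence.

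### The same-day pair is the unit that was randomised, but the stated model, its fallback and the power calculation make no allowance for pairing

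*Protocol article*

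**What the plan says.** **Allocation.** Under Randomisation: "The participants were randomised in sex-matched pairs", and "the randomisation sequence allocated participants attending on the same day to the same study arm". The stated reason is to prevent accidental unblinding during the visit. The abstract adds: "In total, 20 volunteers were randomised in pairs to receive either 8.25 mg dexamethasone or normal saline placebo intravenously". Under Trial oversight, a preliminary analysis at 20 either closes recruitment or leads to an extension: "If not, recruitment will continue to 30 patients".

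**Analysis.** The Statistical analysis plan section gives the reason for a mixed model: "To account for the correlation among measurements taken from the same volunteer at multiple time points". Besides time, the fixed terms are "a fixed term for the treatment group of the volunteer and an interaction term for time and treatment group", plus any baseline characteristic found to be imbalanced. No pair or day term is named. The fallback reads: "If a transformation does not achieve normality, we will use non-parametric methods such as the Mann" (the Mann–Whitney U test is the example given). Tests at 22 h use a 20% level, with 95% confidence intervals.

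**Power.** The Sample size section takes a difference and an SD from an earlier observational study. "It was assumed that dexamethasone will reverse outcome measures to their baseline values". It gives no N, no design effect and no intra-pair correlation.

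**The concern.** Two people attending on the same day can never be in different arms. Anything that makes them alike also makes their outcomes alike within one arm. They share the calendar day and their sex, and may share session conditions. Lake Louise scores are self-reported, so two people spending the same day on the study may influence each other.

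An analysis with volunteers as the independent units then credits the arm comparison with more information than it has. P values come out too small and intervals too narrow. The preliminary analysis at 20 feeds the decision on extending to 30, so if it uses the stated model the understated standard errors reach that decision too.

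**Working it through.** **1. Reproduce Table 1.** For two arms of *n* independent volunteers, a two-sided normal test has power Φ(λ − z), with λ = difference / (SD·√(2/*n*)).

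- Whole-brain ADC, *n* = 12: λ = 0.5 / (0.45 × √(2/12)) = 2.72, giving 77.7 / 85.9 / 92.5% at α = 0.05 / 0.10 / 0.20. Table 1 states 78 / 86 / 93.
- Corpus callosum ADC, *n* = 12: λ = 1.35 / (1.65 × √(2/12)) = 2.00, giving 51.8 / 64.0 / 76.5%. Stated: 52 / 64 / 77.
- Blood oxygen content, *n* = 12: 96.5 / 98.3 / 99.4%. Stated: 97 / 98 / 99.

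All nine entries agree within 0.5 points at 12 per arm. At 10 per arm (20 volunteers) whole-brain ADC gives 70.0 / 79.9 / 88.6% and corpus callosum 44.8 / 57.3 / 70.8%, so the table does not reproduce there. The calculation behind it assumes independent volunteers, at about 12 per arm.

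**2. Error of a volunteer-level test.** Inputs: 20 volunteers in pairs (abstract); 5 v 5 pairs (assumes 1:1); ICC ρ from 0 to 0.5 (assumed). The test is an ordinary t-test at one time point with 18 df.

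The true variance of the arm difference is (2σ²/10)(1 + ρ). The t-test estimates (2σ²/10)(1 − ρ/9) on average. At ρ = 0.3 the ratio is 1.3 / 0.967 = 1.345, so the standard error is too small by a factor of √1.345 = 1.16. The nominal 20% cut-off of 1.330 then acts as 1.330 / 1.16 = 1.15, which gives a two-sided error of about 27%. Simulation of 200,000 null trials per ICC gives:

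| ICC | True error at nominal 20% | True error at nominal 5% |
|---|---|---|
| 0 | 20% | 5% |
| 0.1 | 22% | 6% |
| 0.3 | 27% | 9% |
| 0.5 | 31% | 12% |

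A t-test on pair means (8 df) holds 20% and 5% throughout. The 5% column bears on the coverage of the 95% intervals.

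**3. Power with the pair as the unit.** A pair mean has variance SD²(1 + ρ)/2. With 5 v 5 pairs the noncentrality is difference / (SD·√((1 + ρ)/5)), on 8 df; the two-sided 20% cut-off is 1.397. For whole-brain ADC at ρ = 0.3 this is 0.5 / (0.45 × √0.26) = 2.18, giving 78%.

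| α = 0.20 | Stated | ICC 0 | 0.1 | 0.3 | 0.5 |
|---|---|---|---|---|---|
| Blood oxygen content | 99 | 97.6 | 96.6 | 94.3 | 91.6 |
| Whole-brain ADC | 93 | 85.8 | 83.2 | 78.3 | 73.9 |
| Corpus callosum ADC | 77 | 67.5 | 64.6 | 59.7 | 55.7 |

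**4. Split the gap.** For whole-brain ADC: 93 stated; 88.6 with 10 rather than 12 per arm (normal); 87.4 with a t-test on 18 df; 85.8 on 8 df at ICC 0; 78.3 at ICC 0.3. So 85.8 − 78.3 = 7.5 points come from an ICC of 0.3 and 87.4 − 85.8 = 1.6 from the lost degrees of freedom. The other 93 − 87.4 = 5.6 come from the N behind the table and the normal approximation.

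**The case against.** The strongest reply is that this is a condensed article on a declared pilot. It lists fixed terms and no random effects, so a pair term is absent but not excluded, and Mann–Whitney is only an example. With pairs of two the design effect, 1 + ICC, cannot exceed 2. At ICC 0.1 the error is 22% against 20%. The t-test above is also not the planned mixed model.

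Much of this stands as a limit on size. The percentages illustrate the problem and are not the planned model's error rates. Shared tent, staff or scanner session is not documented, and inspired gases are monitored closely. But the article does say which correlation the model is there to handle, and it is the within-volunteer one alone. Using all time points does not help, because the target is the arm difference at 22 h and a pair effect does not cancel from it. Pilot status justifies a lenient level, not a level that differs from the one stated.

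A reader might also infer that sex matching leaves the arms unbalanced by sex, since both members of a same-sex pair go to one arm. The documents do not support that. Allocation used blocks whose size and strata are not given, the numbers of male and female pairs are not stated, and the analysis adds a fixed term for an imbalanced baseline characteristic, with gender among those compared.

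**Conclusion.** The point holds: allocation is by same-day pair, and neither the stated model, the named fallback nor Table 1 allows for it. Its size depends on an ICC that the documents do not give. Over an assumed 0.1 to 0.5, a nominal 20% volunteer-level test runs at about 22% to 31%, and a nominal 5% test at about 6% to 12%. The working also assumes exactly two volunteers per day, a 1:1 ratio and a stop at 20. An extension to 30 gives 15 pairs, which cannot split equally.

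Three stronger readings should be resisted:

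- That inference is wrong for every outcome. The excess exists only where pair members are correlated; at ICC 0 there is none.
- That the treatment estimate is biased. Because pairs were randomised, the fault lies in the standard error.
- That Table 1 was computed for 20 volunteers. It states no N and matches about 24 (12 per arm), so not all of the power shortfall is due to pairing.

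**What to change.** - **Model.** Add a random effect for pair (session day) to each mixed model, alongside the volunteer effect, with Kenward–Roger or Satterthwaite degrees of freedom. With 10 pairs the arm contrast has about 10 − 2 = 8.
- **Fallback.** Replace the Mann–Whitney test with a permutation test that permutes arms over pairs, within the blocks actually used. An unrestricted 5 v 5 split has 252 allocations.
- **Power.** Restate Table 1 with its N, the pair as the unit and a range of ICCs.
- **Preliminary analysis.** Use the same pair-level model for the look at 20.

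The same-day allocation can stay, since it protects blinding, and no new data are needed. The cost is wider intervals, lower stated power and a pair variance estimated imprecisely from about 10 pairs. That estimate may come out at zero, in which case the t-test on pair means at 22 h (8 df) is a useful check.
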